## Methods/Design

### Design

This is a randomized, controlled trial, single-blinded for participants for two of the four treatment options (sham ultrasound and ultrasound) (Figure 1). Recruited patients undergo telephone screening followed by a clinical examination by a medical doctor to ensure eligibility. Eligible participants then undergo outcome assessment using the complete test battery prior to intervention, and will subsequently be randomized to one of the four groups. A ratio of 10:10:10:1 will be used for randomization into Hip School (HS), no intervention group (CO), sham ultrasound group (SUS), and ultrasound group (US). During the 12 week intervention period, monthly logbooks for physical exercises and pain have to be completed by all subjects. The complete test battery is repeated after the 12 week interventional period. Questionnaires (WOMAC, SF36) and log books are accessed via telephone assessment 16 and 40 weeks after the retest.

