### Proposed sample size/power calculation

The primary endpoint is the change of SF36: Subscale bodily pain from M1 to M2 of HS in comparison to CO. Responsiveness of the subscale is comparable to the pain scale of the disease specific WOMAC in patients with osteoarthritis undergoing a rehabilitation intervention [52]. The SF36 is recommended as a generic instrument for recording relevant domains in osteoarthritis of the lower limb [53]. It is the most widely used generic health instrument [52] and allows comparison of disease states within and between different disorders.

Sample size calculation is based on clinically relevant changes: An effect smaller than the minimum clinical important difference (MCID) may be measureable although patients will be unable to notice it [50]. MCID was derived from literature [50], basic values and statistical spread of the measure for the given population were derived from a pilot study of our own research group on subjects with hip osteoarthritis. According to the mentioned presumptions, a sample size of n = 60 in each group will have 80% power to detect a clinically relevant difference in bodily pain for HS in comparison to CO using a two group t-test with a 0.05 two-side significance level. A failure rate of 15-20% is approximated, thus final sample size is set at n = 70 for each group, except US with n = 7. This is only an explorative intervention. Sample size was calculated using G*Power Version 3.0.10 (Franz Faul, Universitaet Kiel, Germany).

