### Statistical analysis

Data will be analyzed on an intention-to-treat principle using all randomized participants. Missing data will be filled in by carrying the last score forward. A per protocol analysis will also be conducted as a subordinate type of analysis. Demographic characteristics, joint and muscle function, and logbooks will be displayed with descriptive statistics. Multivariate statistics will be used (factors: group × time) for outcomes measured on a continuous scale. For strength measures, baseline levels will be included as covariates.

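### Baseline is named as a covariate for strength only; adjusting the primary bodily-pain comparison for its M1 score would be more precise at almost no cost

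*Protocol article*

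**What the plan says.** Two sections of the protocol article bear on this.

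- **Proposed sample size/power calculation** defines the endpoint: "The primary endpoint is the change of SF36: Subscale bodily pain from M1 to M2 of HS in comparison to CO". The power statement is that "a sample size of n = 60 in each group will have 80% power to detect a clinically relevant difference in bodily pain", "using a two group t-test with a 0.05 two-side significance level". No covariate enters that calculation.
- **Statistical analysis** gives group and time as the factors of the model for continuous outcomes. Its only mention of baseline adjustment is: "For strength measures, baseline levels will be included as covariates".

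The SF36 is completed at M1 and M2 (Outcome measures). Participants meet the questionnaires before treatment is allocated (Blinding), and the allocation list is consulted only at the end of the baseline visit (Randomization process and allocation concealment). M1 bodily pain is therefore available as a clean pre-allocation covariate.

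**The concern.** Baseline adjustment was considered and adopted for a secondary outcome family, but it is not named for the primary outcome. An unconstrained group-by-time model for HS and CO over M1 and M2 has an interaction test identical to the t-test on raw change. The sample size section and the analysis section then agree with each other, and both point to unadjusted change.

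Two things are at stake:

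- **Precision.** Raw change subtracts the whole baseline score, although with equal variances the M2 score follows the M1 score only with slope rho. The excess adds noise.
- **Chance imbalance.** If the arms happen to differ by D at M1, the expected change contrast given D is the treatment effect minus (1-rho)D. At rho = 0.5, half of any chance baseline difference passes into the estimate. ANCOVA removes this.

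**Working it through.** **Inputs from the article.** 60 per arm, 80% power, two-sided 0.05, two-group t-test (Proposed sample size/power calculation). HS and CO are allocated 1:1 ("A ratio of 10:10:10:1 will be used for randomization").

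**Inputs the article does not give.**
- The size of the effect: "MCID was derived from literature [50" comes with no value.
- The SD: "basic values and statistical spread of the measure for the given population were derived from a pilot study of our own research group" gives no value, and does not say whether it is the SD of the score or of the change.
- The M1-M2 correlation rho, taken here as an assumption over 0.3 to 0.8.

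**The plan's own figure.** Without a difference and an SD, 60 per arm cannot be reproduced; it can only be back-solved.
- Normal approximation: d = (1.960 + 0.842) × √(2/60) = 0.511.
- Noncentral t: d = 0.516, used below.

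**Variance ratio.** With variance s² at both visits:
- Raw change: 2s²(1-rho).
- M2 adjusted for M1: s²(1-rho²).
- Ratio: (1-rho²) / [2(1-rho)] = (1+rho)/2, which is below 1 whenever rho is below 1.

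For rho 0.4 to 0.7 the ratio is 0.70 to 0.85. Unadjusted change then needs 1/0.85 = 1.18 to 1/0.70 = 1.43 times as many participants for the same precision.

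**Reading A: the planned 80% refers to the SD of change.** Change has d = 0.516; ANCOVA has d = 0.516/√[(1+rho)/2].

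| rho | variance ratio | power, change, 60/arm | power, ANCOVA, 60/arm | n/arm for 80% with ANCOVA |
|---|---|---|---|---|
| 0.3 | 0.65 | 80% | 93.5% | 40 |
| 0.4 | 0.70 | 80% | 91.8% | 43 |
| 0.5 | 0.75 | 80% | 89.9% | 46 |
| 0.6 | 0.80 | 80% | 87.9% | 49 |
| 0.7 | 0.85 | 80% | 86.0% | 52 |
| 0.8 | 0.90 | 80% | 84.0% | 55 |

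A simulation at rho = 0.5 (4000 runs, 60 per arm) gave 80.9% for change and 90.4% for ANCOVA, in line with the table.

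**Reading B: the pilot spread is the SD of the score.** Change has d = 0.516/√[2(1-rho)]; ANCOVA has d = 0.516/√(1-rho²).

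| rho | power, change, 60/arm | power, ANCOVA, 60/arm | gain (points) |
|---|---|---|---|
| 0.3 | 65.8% | 83.6% | about 18 |
| 0.5 | 80.0% | 89.9% | about 10 |
| 0.7 | 95.1% | 97.5% | about 2 |

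The two readings coincide at rho = 0.5, where 2(1-rho) = 1. Under Reading B the starting power is not fixed at 80%.

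**Not modelled.** The plan fills missing values with the last score, which sets change to zero for anyone without an M2 score. That affects the effect and the variance in both analyses. All figures above assume 60 per arm with both scores observed.

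**The case against.** The strongest reply is that nothing here is an error. Under randomisation the comparison of change is unbiased and holds its type I error. Endpoint, sample size and analysis agree, and if the pilot SD was that of change, the planned 80% is delivered. This stands: the point concerns efficiency, and the comparison is with a better model rather than a correct one. A reader might infer from the regression-to-the-mean argument that the primary result would be biased. It would not; that argument is conditional on an observed imbalance and averages out over randomisation.

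Second, the article never states outright that bodily pain is unadjusted. It does not say which visits and arms enter the model. The SF36 is also taken at M3 and M4, and a longitudinal model with a common baseline mean would fit the wording and have ANCOVA-type efficiency. A full analysis plan, not shown, may specify this. So unadjusted change is an inference. It remains the natural reading, because the text gives a method and limits the baseline covariate to strength.

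Third, a reader might infer that strength is modelled with baseline counted twice, once as a level of time and once as a covariate. The documents do not support that. Strength is measured only at M1 and M2, and the sentence reads equally well as an ANCOVA of the M2 value. Nothing says that M1 also stays in as a response.

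Fourth, extending adjustment to every continuous outcome would go too far. Gait time histories are not single scores, and joint and muscle function are to be described only.

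**Conclusion.** The point holds as one of avoidable imprecision in a valid analysis. Read together, the two sections make the primary HS-CO comparison most naturally one of unadjusted change. Adjusting for M1 bodily pain would cut the variance of the estimate to 0.70-0.85 of its value for rho 0.4-0.7, and would protect against chance baseline imbalance.

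The variance ratio assumes equal variances at M1 and M2 and an assumed rho. The power gain also depends on which SD the pilot supplied: from 80% to about 86-92% for rho 0.4-0.7 if it was the SD of change, and from about 18 points (rho 0.3) to about 2 points (rho 0.7) if it was the SD of the score. No single figure for the gain can be given, and it shrinks as rho approaches 1.

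**What to change.** State in Statistical analysis that the primary analysis is an ANCOVA of M2 bodily pain, or an equivalent mixed model, with M1 bodily pain as covariate and HS versus CO as the primary contrast. Report the adjusted difference with its 95% CI. Apply the same model to the other scalar continuous outcomes that are formally tested, such as WOMAC and the remaining SF36 scales. It would also help to say whether the pilot spread is the SD of the score or of the change, and what M1-M2 correlation the pilot showed, so that the expected gain can be calculated.

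The cost is a sentence or two and one degree of freedom. No extra data or participants are needed, and the sample size can stay as it is.
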